## Abstract

**Background:**

Visual Rehabilitation Officers help people with a visual impairment maintain their independence. This intervention adopts a flexible, goal-centred approach, which may include training in mobility, use of optical and non-optical aids, and performance of activities of daily living. Although Visual Rehabilitation Officers are an integral part of the low vision service in the United Kingdom, evidence that they are effective is lacking. The purpose of this exploratory trial is to estimate the impact of a Visual Rehabilitation Officer on self-reported visual function, psychosocial and quality-of-life outcomes in individuals with low vision.

**Methods/design:**

In this exploratory, assessor-masked, parallel group, randomised controlled trial, participants will be allocated either to receive home visits from a Visual Rehabilitation Officer (*n* = 30) or to a waiting list control group (*n* = 30) in a 1:1 ratio. Adult volunteers with a visual impairment, who have been identified as needing rehabilitation officer input by a social worker, will take part. Those with an urgent need for a Visual Rehabilitation Officer or who have a cognitive impairment will be excluded. The primary outcome measure will be self-reported visual function (48-item Veterans Affairs Low Vision Visual Functioning Questionnaire). Secondary outcome measures will include psychological and quality-of-life metrics: the Patient Health Questionnaire (PHQ-9), the Warwick-Edinburgh Mental Well-being Scale (WEMWBS), the Adjustment to Age-related Visual Loss Scale (AVL-12), the Standardised Health-related Quality of Life Questionnaire (EQ-5D) and the UCLA Loneliness Scale. The interviewer collecting the outcomes will be masked to the group allocations. The analysis will be undertaken on a complete case and intention-to-treat basis. Analysis of covariance (ANCOVA) will be applied to follow-up questionnaire scores, with the baseline score as a covariate.

**Discussion:**

This trial is expected to provide robust effect size estimates of the intervention effect. The data will be used to design a large-scale randomised controlled trial to evaluate fully the Visual Rehabilitation Officer intervention. A rigorous evaluation of Rehabilitation Officer input is vital to direct a future low vision rehabilitation strategy and to help direct government resources.

**Trial registration:**

The trial was registered with (ISRCTN44807874) on 9 March 2015.

## Background

Low vision is associated with depression [1, 2], reduced quality of life [2, 3] and reduced mobility [2, 4, 5]. Low vision rehabilitation is defined as an amelioration of the lives of individuals with sight loss by improving functional ability and other general aspects, for example, quality of life and psychosocial status [6]. It represents a range of services that operate at the interface of health and social care services to minimise disability and promote independent living. In the United Kingdom, health-based services attempt to help those with low vision make the best use of their remaining eyesight by providing optical and non-optical low vision aids, advice on lighting and contrast enhancement, and onward referral, where appropriate. Social care services tend to take a more holistic approach based on a comprehensive needs assessment, often in the person’s own home. This can result in modifications to the home environment, provision of non-optical aids, mobility training and advice on benefits. Visual Rehabilitation Officers are trained professionals with a 2-year foundation or 3-year degree qualification, who work with people in their homes, often over several sessions, facilitating the learning of new strategies, which include, for example, how to navigate safely, identify objects, read instructions, the use of low vision aids and non-optical aids. A list of further examples is provided in Table 1.

**Table 1 Tab1:** Summary of support by the Visual Rehabilitation Officer. The table summarises general areas assessed by the Visual Rehabilitation Officer and examples of provision of training and support in each area

Area assessed	Examples of support
Emotional• Emotional state of participant and family • How family members cope with adjustment to the participant’s sight loss.	• Education on eye condition and related emotional, practical and physical difficulties.• Sign-posting to other organisations that can provide emotional support.
Low Vision Function• Functional vision assessment• Best contrast/colour contrast to assist practice in daily living.• Glare sensitivity.	• Eccentric viewing or steady eye strategy training and scanning techniques.• Provision of tinted glasses/peak cap. Training in techniques/aids for watching television.• Training on use of low vision aids, issued by the optometrist• Referral to optometrist.
Lighting• Lighting assessment for areas in and around home	• Provision of specific task lamps, specialist light bulbs.
Personal• Potential difficulties with dressing, grooming and personal hygiene.	• Provision of strategy for identifying and matching colour of clothing, makeup application, hair management, shaving, application of toothpaste on tooth brush, identifying bottles and contents, feminine intimate care.
Medication• Ability to manage medication independently.	• Provision of strategy to administer eye drops, dispense pills from blister packs, systematically search for dropped pill• Provision of dosset boxes, enlarged labels.
Kitchen• Potential difficulties with cooking and meal preparation.	• Training and provision of equipment for cooking. For example, for pouring liquids, knife management and other safety aspects, sequence/timing strategy.
Home• Potential difficulties with household chores, for example, cleaning, tidying, laundry, bed making.	• Training to support tasks such as cleaning, tidying, laundry and bed making. For example, systematic approach for vacuuming and dusting, measuring soap powder/liquid, separating laundry, folding clothing, safe techniques and equipment to avoid burns when ironing, threading needles, changing sheets.
Entitlements• Criteria check for entitlements.	• Assistance with applications. For example, for Disabled Parking badge, bus pass, Disabled rail card, talking magazines/newspapers, British Wireless for the Blind fund, Personal tax allowance, TV licence, accessing utility discount scheme.• Referrals for benefits assessments.
Referrals• Possible need for referral to specialist service.	• Referral to appropriate agency. For example, Occupational therapist, Physiotherapy, Age Concern, Cardiff Institute for the Blind, GP, Diabetic Nurse, Opticians for Wales Eye Care Low Vision Scheme, CAB, Action for Blind, RNIB Benefits, Speech Therapists, Support Groups, talking books, Care & Repair, Sense Cymru, Befriending, Talk and Support, refer to Sight Cymru BME advisor, Highway Maintenance, Hearing Team Cardiff Social Services.
Orientation and Mobility• Potential orientation and mobility difficulties.	• Long cane training, symbol cane issuing and sighted guide training, guide cane training, route and orientation training.• Support for planning travel arrangements. For example, timetables, relevant platform/bus stop/departure gate, arrangements for company provision of Travel Assistance, etc.
Communication• Potential difficulties with telephones, appointments, correspondence, finance management, IT.	Support and advice on the following:• Appropriate telephones and related devices.• Telephone banking, telephone/online shopping.• Note taking and maintaining appointments diary (large print, address guides).• Techniques or equipment suitable to needs for reading, general correspondence, telling the time.• Strategy for accessing bank and money management• Computer technology assistance and referral for IT skills training.

There is evidence that impaired functional status in individuals with visual loss is associated with depression [7–9], psychosocial impact [10–12], risk of falls, decreased mobility [13–15] and higher rates of mental and physical health comorbidities. Partial evidence exists of improved health-related quality-of-life outcomes following visual rehabilitation intervention [16, 17] and improvement in vision-related quality-of-life following visual rehabilitation [16, 18–20]. However, a paucity of high-quality evidence exists regarding the effectiveness of low vision rehabilitation services, particularly with regard to social care provision [6].

The need for evidence to support the low vision rehabilitation service is driven by the necessity to inform direction for healthcare resources, as a result of the growing social and economic challenges faced by those with visual impairment [6]. The burden on such resources is growing with the increase in the elderly population and therefore, the increasing number of individuals with low vision. The evidence gained from this study will inform the design of a definitive trial, which will help shape the development of low vision rehabilitation services in the UK.

The primary aim is to examine the effect of a Visual Rehabilitation Officer intervention (ROI) on self-reported visual function. The secondary aims are to determine the effect of the low vision rehabilitation service on depression, well-being, loneliness, adjustment to visual loss and generic health-related quality-of-life. The relation between the numbers of intervention items received on the outcomes will also be assessed.

## Methods/design

This exploratory assessor-masked individually randomised single centre controlled trial is designed to give robust estimates of the effect of a ROI on self-reported functional, psychosocial and quality of life outcome measures. Participants will be allocated to the ROI or waiting list arms of the trial in the ratio 1:1. The trial will be carried out over 18 months (see flow diagram in Fig. 1).

**Fig. 1 Fig1:**
[figure not shown]
Study flow diagram

The Research Ethics Audit Committee, at the School of Optometry and Vision Sciences, Cardiff University reviewed and approved the study (#1377).

### Intervention

There is one active intervention in the trial, that is, the ROI. In one to eight sessions, a Visual Rehabilitation Officer will conduct home visits to assess the status of the individual with low vision and provide training and support in specific areas of need.

The support is tailored to the individual in a number of areas including mobility, use of low vision aids, household tasks, communication and administrative tasks. Table 1 details the types of intervention that may be provided by the Visual Rehabilitation Officer. Not all components are provided to each person, because the ROI is tailored to meet individual requirements (Table 1). The aim of the rehabilitation is to promote independence by helping individuals learn new skills or regain lost skills and rebuild confidence following sight loss. This support may be implemented by the provision of information, equipment, encouragement, training and/or referral to other agencies. This type of intervention is typical of that provided by Visual Rehabilitation Officers in the UK.

For each participant in the intervention arm, a list of intervention items implemented and the number of visits will be recorded, by the Visual Rehabilitation Officer (Table 2). In this trial, participants will be recruited from South East Wales. The intervention will be provided by a team of two experienced Visual Rehabilitation Officers (each with 7 to 8 years of experience) based at the Sight Cymru rehabilitation service. This service was chosen for its proximity to the research centre at Cardiff University and the willingness of the service to support a rigorous research study.

**Table 2 Tab2:** List of intervention items recorded by the Visual Rehabilitation Officer

Intervention items:
Initial assessment
Functional vision assessment
Low vision training/advice
Magnification advice
Lighting advice
Personal care/medication advice
Washing and dressing
Medication management
Kitchen skills
Safe pouring technique
Food preparation/cooking
Cleaning/managing the home
Laundry
Ironing
Money issues
Orientation and mobility training
Road safety check
Sighted guide technique
Symbol cane advice
Guide cane training
Long cane training
Communications
Reading and writing
Accessing TV and radio
Using phones
Telling the time
Audio books
IT
Social and leisure activities
Emotional well-being
Referrals to other agencies (specified)
Other (specified)

The second arm of the study is a ‘waiting list control’ group, consisting of individuals on the existing Sight Cymru waiting list for the visual rehabilitation service. The ‘waiting list control’ provides individuals electing to take part in the study with a better level of care than ‘treatment as usual’ because the service will be received on completion of the study, that is, after 6 months, which is sooner than for those on the existing waiting list.

### Outcome measures

Outcome measures will consist of the questionnaires administered at baseline and 6 months (±1 month) follow-up. The primary outcome measure will be the 48-item Veterans Affairs Low Vision Visual Functioning Questionnaire (VA LV VFQ-48), a validated unidimensional functional outcome measure questionnaire that assesses the difficulty in performing daily activities in visually impaired individuals [21]. Secondary outcome measures will include: the Patient Health Questionnaire (PHQ-9), an assessment of depression symptom severity on a nine-item scale, based on criteria for depressive episodes including concentration problems and suicide [22]; the Warwick-Edinburgh Mental Well-being Scale (WEMWBS), a population measure of subjective well-being, involving 14 positively worded questions about aspects of positive thoughts and feelings [23]; the Adjustment to Age-related Visual Loss Scale (AVL-12), a measure of psychological adjustment to vision loss [24]; the standardised Health-related Quality of Life Questionnaire (EQ-5D), a ‘utility’ measure to assess five health-related dimensions, that is, mobility, self-care, usual activities, pain/discomfort and anxiety/depression [25]; and the UCLA Loneliness Scale, a 20-item scale to measure subjective feelings of loneliness and social isolation [26].

These instruments were selected on the basis of the following evidence. The VA LV VFQ-48 has been assessed as a high-quality instrument for use in evaluating adults with low vision [27]. The PHQ-9 is a suitable measure of depressive symptoms in those with visual loss [28]. Mental well-being is a prominent issue in governmental health policy, and the utility of the WEMWBS has been demonstrated in general populations [29]. The AVL-12 has been adopted effectively in several trials of individuals with low vision following rehabilitation [30–32]. Whilst the EQ-5D may be unresponsive to low vision rehabilitation [33], it is the preferred measure of health utility by the National Institute of Clinical Excellence guidance (NICE article PMG9, 2013). It is acknowledged that health disorders are risk factors for loneliness [34], and the UCLA scale has been used to evaluate individuals with low vision [35].

Outcome measures will be obtained over the telephone by a trained interviewer who will be masked to the group allocation. The order of outcome measures will be partially randomised with a pre-determined order, such that the PHQ-9 and UCLA scale (negatively worded) should be performed before the WEMWBS (positively worded), in order to position a positively worded questionnaire at the end of the interview. However, it must be acknowledged that this may affect the quality of responses to the WEMWBS. Whilst participants will be encouraged not to reveal any information about their group allocation during telephone interviews, any masking violations will be recorded. The success of masking will be assessed, by requiring the interviewer to guess the allocation prior to the start of the final 6-month follow-up. All responses will be coded and double entered.

### Sample size

On the basis of a conservative effect size determined by the VA LV VFQ-48 item scores in a previous study [36], a sample of 30 participants in each group at follow-up can be expected to detect a standardised difference of 0.84 logits between those in the intervention and control groups, with 95 % power and an alpha level of 0.05 (two-tailed). To allow for individuals who may withdraw from the study (approximately 15 %), a total of 70 individuals will be recruited.

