Baseline characteristics will be summarised by descriptive statistics. Questionnaire scores at follow-up will be analysed using analysis of covariance (ANCOVA), controlling for the baseline score and the key variables (age, co-morbidities and visual acuity) as covariates. A logistic regression analysis will investigate whether the number of intervention items is associated with the outcomes. Standard diagnostics will be used to check model fit (for example, residual versus fitted plots), and standard transformations (square root, log and square) explored where necessary. The analysis will be complete case and intention to treat. This exploratory study is not powered to identify statistically significant differences; therefore, the results will be interpreted using descriptive statistics and 95 % confidence intervals.

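### The stated 95% power does not follow from 30 per group and a standardised difference of 0.84 (about 89%), and the Analysis section contradicts the power claim

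*Protocol article*

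**What the plan says.** The Sample size section of the protocol article makes a complete power claim for the primary outcome, the VA LV VFQ-48. It states that "a sample of 30 participants in each group at follow-up can be expected to detect a standardised difference of 0.84 logits", with 95% "power and an alpha level of 0.05 (two-tailed"). The effect size is attributed to a previous study. For withdrawals the section adds: "approximately 15 %), a total of 70 individuals will be recruited".

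The Methods/design section fixes equal allocation: "Participants will be allocated to the ROI or waiting list arms of the trial in the ratio 1:1".

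The Analysis section names the model: "Questionnaire scores at follow-up will be analysed using analysis of covariance (ANCOVA), controlling for the baseline score", with age, co-morbidities and visual acuity as further covariates. It ends by saying: "This exploratory study is not powered to identify statistically significant differences". For that reason, results are to be interpreted with descriptive statistics and 95% confidence intervals.

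The article gives neither an SD for the primary outcome nor a correlation between baseline and follow-up scores.

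**The concern.** Three things do not fit together.

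- **The power figure.** The inputs needed for a two-group calculation are all stated, yet they do not return 95%.
- **The unit.** The phrase "a standardised difference of 0.84 logits between those in the intervention and control groups" attaches a unit to a quantity that has none. Under Analysis, the primary outcome is Rasch-analysed and logits are its measurement scale, so a raw difference in logits is a natural alternative reading. The two readings agree only if the SD is 1 logit.
- **The contradiction.** One section claims high power at a two-tailed significance level. The other says the study is not powered to find significant differences and makes no exception for the primary outcome.

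A reader of a null result could not tell whether the plan regarded the trial as able to detect the target effect. The article also says these data will be used to design a large-scale trial, so an undefined effect unit and an unsupported power figure could be carried forward.

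**Working it through.** **Inputs.** From Sample size: n = 30 per group at follow-up, difference 0.84, two-tailed alpha 0.05, stated power 95%, about 15% withdrawal, 70 recruited. From Methods/design: 1:1 allocation.

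**Step 1: the plan's figure, with 0.84 in SD units and no covariate adjustment.**
- Noncentrality = d × √(n/2) = 0.84 × √15 = 3.253, with df = 2 × 30 − 2 = 58.
- The two-sided 5% critical value of t on 58 df is 2.002.
- Power from the noncentral t distribution is **89.2%**. The normal approximation, Φ(3.253 − 1.960), gives 90.2%.
- Type II error on this reading is 100 − 89.2 = 10.8%, against the stated 5%.

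The 95% is not reproduced.

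**Step 2: what would give 95% on the same reading.**
- Group size: 2 × (1.960 + 1.645)² / 0.84² = 36.8, so 37 per group by normal approximation. By noncentral t, 37 gives 94.6% and 38 gives 95.1%, so 38 are needed.
- Difference detectable with 30 per group: (1.960 + 1.645) × √(2/30) = 0.93 SD by normal approximation, or 0.95 SD by noncentral t.

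**Step 3: is attrition the explanation?** No. The claim refers to 30 per group at follow-up. Even if all 70 recruited were retained (35 per group), power would be 93.4%. The recruitment figure itself is consistent: 70 × 0.85 = 59.5, or about 60 at follow-up.

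**Step 4: could the planned ANCOVA explain it?** Adjusting for a baseline score with correlation r multiplies the residual SD by √(1 − r²), so the effective difference is 0.84 / √(1 − r²), with df = 57. The article gives no r, so these values are assumptions:

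| Assumed r | Power |
|---|---|
| 0 | 89.2% |
| 0.3 | 91.8% |
| 0.4 | 93.7% |
| 0.46 | 95.0% |
| 0.5 | 95.8% |
| 0.6 | 97.9% |

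**Step 5: could raw logits explain it?** If 0.84 is in logits, d = 0.84 / SD. Power reaches 95% when SD ≤ 0.84 / 0.947 = 0.89. The article gives no SD, so these values are assumptions:

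| Assumed SD (logits) | d | Power |
|---|---|---|
| 0.89 | 0.94 | 95% |
| 1.0 | 0.84 | 89% |
| 1.2 | 0.70 | 76% |
| 1.5 | 0.56 | 57% |

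**Step 6: the two sections side by side.** Sample size: 95% power at "an alpha level of 0.05 (two-tailed"). Analysis: "This exploratory study is not powered to identify statistically significant differences". Both refer to the same trial, and neither is limited to particular outcomes in a way that would separate them.

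**The case against.** The strongest reply is that 89% is conditional. It assumes that 0.84 is in SD units and that the comparison is unadjusted. The protocol plans a baseline-adjusted ANCOVA, and a correlation of about 0.46 is not implausible. If 0.84 is in raw logits, an SD of about 0.89 makes 95% correct, and a condensed article may leave that SD to the full protocol. This stands in part. It shows that 95% could be recovered, but Sample size invokes neither assumption and calls the difference standardised. The published claim is therefore wrong as written or rests on something not stated.

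It is also fair that the practical consequence is limited. About 89% power is respectable, the aim is estimation, and results will be read from confidence intervals.

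Some stronger readings are tempting but are not supported:

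- **That a one-sided calculation was used.** One-sided power is 94.2%, close to 95%, but the text says two-tailed. A two-sided calculation at 90% power needs 2 × (1.960 + 1.282)² / 0.84² = 29.8 per group, which also rounds to 30. The origin of the figure cannot be determined.
- **That the chance of missing the planned effect is twice what is stated.** The 10.8% against 5% holds only for an unadjusted test with 0.84 in SD units.
- **That the effect size is not conservative.** The article uses that word in relation to a cited study that is not available here. The trial it reports as showing no effect is described as testing an add-on to clinic care, so it does not settle the question.
- **That the plan disclaims all power.** The Analysis section says only that the study is not powered for statistically significant differences.

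**Conclusion.** The concern holds, at moderate severity. Taken as a standardised difference in an unadjusted two-sided comparison, the stated inputs give about 89% power (90% by normal approximation), a shortfall of 5 to 6 percentage points from 95%. With 30 per group, 95% power is reached at about 0.95 SD. At 0.84 it requires an assumption missing from the article: a baseline–follow-up correlation of about 0.46 or more, or an SD of about 0.89 logits or less if the difference is raw. The contradiction between Sample size and Analysis does not depend on which reading is right. The design is not undermined, because the trial is exploratory and will be interpreted by confidence intervals.

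**What to change.** Keep the sample size and change the text:

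1. In Sample size, say whether 0.84 is in SD units or logits. If logits, give the SD.
2. Either restate the power as about 89% at 0.84 SD (two-sided 5%, 30 per group at follow-up), or equivalently 95% at 0.95 SD; or keep 95% and state the SD or the baseline–follow-up correlation that produces it, naming the ANCOVA as its basis if the correlation is used.
3. In Analysis, replace the closing statement on power with one that agrees with Sample size, for example: powered only for a large effect on the primary outcome; results interpreted by 95% confidence intervals.

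The cost is wording only. No extra participants are needed, and the published power figure may become slightly less favourable.
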